Although it is plausible that cytokines play a role in the pathophysiology of CFS, there is only indirect evidence for this theory:The complaints of patients with CFS are often described as that of a persistent flu. During infections like influenza, symptoms are generally ascribed to the action of cytokines (like IL-1, IL-6, tumor necrosis factor alpha (TNF) and interferons) [9].Many disease states are accompanied by anorexia, loss of interest, somnolence and fatigue, a symptom complex coined as sickness behavior. The cytokines IL-1beta, TNF and IL-6 are thought to be responsible for it. Administration of either IL-1, IL-6, TNF or each of the interferons to humans and animals is accompanied by flu-like symptoms [16–18].Previously, it was reported that IL-8 and IL-10 were significantly elevated in the cerebrospinal fluid in patients with CFS, compatible with induction of IL-1 [19].Beta amyloid precursor protein has also been found to be elevated in the cerebrospinal fluid of CFS patients [20]. Production of this protein is under control of IL-1 and TNF [21–23].Our group has previously established that patients with CFS have a significant loss of gray matter in the brain [24, 25]. This loss of gray matter might be caused by enhanced cytokine activity.

Drugs that interfere with the proinflammatory cytokine IL-1 are commonly used nowadays for a variety of inflammatory disorders [26]. The recombinant IL-1 receptor antagonist (anakinra) reduces the activity of both IL-1α and IL-1ß by binding to the IL-1 receptor. This intervention is highly targeted and hence would allow investigators to draw conclusions regarding the pathophysiology of CFS, and the effect of reducing cytokine concentrations in CFS patients. Moreover, compared to blocking TNF-α or IL-6, blocking IL-1 with anakinra has a long safety recorded with respect to side effects, and is not associated with increased susceptibility to opportunistic infections such as Mycobacterium tuberculosis.

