### Statistical analysis

The primary analysis will be the comparison between the two different treatment groups (anakinra or placebo) at 4 weeks. Data will be analyzed on an ITT basis. Missing values will be replaced using multiple imputation with fully conditional specification with at least five imputations. The imputation method that will be used is predictive mean matching for missing data in primary and secondary outcome measures. Aside from condition, we will use the following variables assessed at baseline to generate the imputations: duration of symptoms, age, BMI and baseline values of the outcome measures.

The results will be analyzed with SPSS for Windows. To determine if there is a significant difference between the intervention arm and placebo condition, ANCOVA will be used with the outcome measure on the second assessment as the dependent measure, the baseline score as the covariate, and condition as the fixed factor [39]. We will test if significant differences exist between both groups in mean age and BMI at baseline, both known to influence circulating cytokine levels. If so, these variables will be entered as covariates in the ANCOVA. When a statistically significant difference is found in the primary analysis, a sensitivity analysis will be performed on the basis of different assumptions about the values of missing data. For the secondary outcome measures, the same analysis will be repeated, but the secondary outcome measures at the second assessment will serve as the dependent variable and the scores at baseline as the covariate.

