### Power calculation

The sample size is based on the fatigue subscale score of the CIS at 4 weeks. In the present study, the power calculation is based on results from comparable studies with CFS patients where fatigue severity was determined with the CIS-fatigue scale [40]. If interleukin-1 plays a central role in CFS symptomatology, we expect a considerable reduction of fatigue following treatment. Assuming a large controlled effect size of 0.85, an alpha of 0.05 and a power of 0.80, 23 patients are needed in each arm of the study. The number of patients can be further reduced by using ANCOVA, with the outcome measure on the second assessment as the dependent measure, the baseline score as the covariate, and condition as the fixed factor. In this kind of trials, ANCOVA yields greater power compared to other statistical methods [39]. Based on the correlation between the pre- and post CIS fatigue scale, the sample size of 23 can be multiplied by 0.883 (1 to 0.342^2^). Including an assumed dropout rate of 20 percent, we will have to include 25 patients in each group to demonstrate a significant difference between the medication group and placebo.

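### The missing-data sensitivity analysis is planned only after a significant primary result, so a null result would be reported with no planned check of the imputation assumption

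*Protocol article*

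**What the plan says.** All of the following is in the protocol article.

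- **Primary test (Statistical analysis).** The arms are compared at 4 weeks on the CIS fatigue subscale: "ANCOVA will be used with the outcome measure on the second assessment as the dependent measure", with the baseline score as covariate.
- **Missing data (Statistical analysis).** "Missing values will be replaced using multiple imputation with fully conditional specification with at least five imputations". The imputation predictors are condition and these baseline variables: "duration of symptoms, age, BMI and baseline values of the outcome measures".
- **Sensitivity analysis (Statistical analysis).** "When a statistically significant difference is found in the primary analysis, a sensitivity analysis will be performed", and its content is to be "on the basis of different assumptions about the values of missing data". No missing-data sensitivity analysis is described for a non-significant result, here or elsewhere.
- **Dropout (Power calculation).** A dropout rate of 20% is assumed, with 25 patients randomised per arm.
- **Use of the result (Background).** The targeted intervention "would allow investigators to draw conclusions regarding the pathophysiology of CFS". The Power calculation section ties the expected effect to the premise that IL-1 is central to CFS symptoms.

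**The concern.** The p-value decides whether the p-value's main untestable assumption is examined. The 4-week score of a patient who leaves is predicted from arm and baseline variables only, so it is assumed to resemble the scores of similar patients who stayed in the same arm. The trial data cannot confirm that.

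If the assumption fails, it can fail in either direction. Outcome-related, arm-dependent dropout is plausible here, although the documents do not establish it: anakinra causes local injection-site reactions, and patients who withdraw are offered CBT. If placebo patients who are not improving leave more often, the remaining placebo mean looks too good and a true effect shrinks.

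What is at stake is the reading of a null result. The article presents this as the first placebo-controlled trial of IL-1 blockade in CFS and intends to draw pathophysiological conclusions, so a null result would be taken as evidence about IL-1. As planned, readers could not tell a true absence of effect from an effect masked by missing data.

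**Working it through.** **Inputs from the documents (Power calculation):** standardised effect 0.85; alpha 0.05 (sidedness not stated; two-sided reproduces the figure); power 0.80; 23 per arm; ANCOVA factor 0.883; dropout 20%; 25 per arm randomised.

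**Assumptions, not in the documents:** a smaller true effect of 0.5; a departure delta of the missing values from the imputation model, taken as 0.5 SD with a range of 0.25 to 1.0 SD; 20 completers per arm as an approximation to the precision of the imputed analysis.

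**1. The plan's own figure.**
- Two-sided two-sample t-test at d = 0.85: n = 22.73, so 23 per arm. The stated figure reproduces.
- "the sample size of 23 can be multiplied by 0.883": 1 − 0.342² = 0.883, and 23 × 0.883 = 20.3.
- 20.3 / 0.8 = 25.4 (25.1 if the 22.73 is carried unrounded), against 25 stated. The design figures are not in dispute.

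**2. How often no check would be done.** With 20 completers per arm, SE = √(0.883 × 2/20) = 0.297 SD. The critical t on 37 degrees of freedom is 2.026, so the significance limit is 2.026 × 0.297 = 0.602 SD.
- d = 0.85: ANCOVA power 0.795, so 1 − 0.795 = 0.205 non-significant.
- d = 0.5: ANCOVA power 0.374, so 1 − 0.374 = 0.626 non-significant.

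**3. How far missing data can move the result.** Shift = share missing × delta. For 20% missing in one arm and delta = 0.5 SD, this is 0.20 × 0.5 = 0.10 SD, and 0.10 / 0.297 = 0.34 SE. If both arms depart in opposite directions, it is 0.20 SD. The p-value does not enter the formula.

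Example: p = 0.08 corresponds to t = 1.80 on 37 df; 1.80 + 0.34 = 2.14, which gives p = 0.039.

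**4. Which results could cross 0.05 (20% missing).**

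| delta (SD) | Arms departing | Shift (SD) | Null becomes significant if p is up to | Significant becomes null if p is down to |
|---|---|---|---|---|
| 0.25 | one | 0.05 | 0.07 | 0.035 |
| 0.25 | both, opposite | 0.10 | 0.10 | 0.024 |
| 0.5 | one | 0.10 | 0.10 | 0.024 |
| 0.5 | both, opposite | 0.20 | 0.18 | 0.010 |
| 1.0 | one | 0.20 | 0.18 | 0.010 |
| 1.0 | both, opposite | 0.40 | 0.50 | 0.002 |

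The same shift in the estimate acts on both sides of 0.05, and the plan examines only one side.

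**5. Share of trials in the crossing zone.** For the 0.10 SD shift, this is the probability that the estimate lies between 0.602 − 0.10 = 0.502 SD and 0.602 SD: about 8% of trials at d = 0.85 and about 13% at d = 0.5.

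**6. Can dropout produce a false negative?** Trials were simulated with true d = 0.85, 5 of 25 missing per arm, an assumed strength of outcome-related dropout, and ANCOVA on completers (the planned imputation was not simulated).

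| Dropout | Mean estimated effect (SD) | Power |
|---|---|---|
| Unrelated to outcome | 0.86 | 0.80 |
| Worse placebo patients leave more often | 0.68 | 0.62 |
| Also, better anakinra patients leave more often | 0.51 | 0.43 |

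**The case against.** The strongest case on the other side has four parts.

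- **The 20% and 63% are just one minus power.** That is correct. They count trials that get no check, not trials whose conclusion would change. The crossing share for a 0.10 SD shift is about 8% and 13%. Both pairs are needed, and the smaller pair measures the practical effect. The one-arm example is also slightly mixed: with 5 missing in one arm only, the SE is √(0.883 × (1/20 + 1/25)) = 0.282, not 0.297. The shift is then 0.35 SE instead of 0.34, which changes nothing material.
- **Dropout is not the same as a missing primary outcome.** The CIS is a web-based questionnaire, the endpoint comes at only 4 weeks, and the withdrawal section promises efforts to keep measuring after discontinuation. So 20% missing is better read as an upper planning figure, and lower missingness shrinks every shift in proportion: at 10% missing and delta 0.5 SD, one arm moves by 0.05 SD. This stands, but it limits the amount missing without testing the assumption about what remains missing.
- **The asymmetry has a rationale.** The confirmatory aim is to show a reduction in fatigue, no claim of no effect is planned, and a false positive is often thought costlier. That is a reason to stress-test a positive result; it gives no reason to leave a null one untested. The Background sentence on pathophysiology explains the choice of a targeted drug and does not itself speak of a null result, but together with the IL-1 premise under Power calculation it shows that a null would bear on the hypothesis.
- **Details of a sensitivity analysis belong in the SAP.** This is true of the delta values and the tipping-point design. The condition itself is written in the article, so it is not something left to the SAP.

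Two limits of wording also follow. The calculation shows that a null result is as exposed as a positive one, not more. And the plan omits a check after a null result; it does not forbid one.

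**Conclusion.** The concern holds. The rule is explicit, and it leaves every non-significant primary result without a planned missing-data check: about 20% of trials at the design effect and about 63% at an assumed effect of 0.5, with 20 completers per arm. Under an assumed one-arm departure of 0.5 SD with 20% missing, about 8% and 13% of trials respectively would be null results near enough to 0.05 to cross it. The effect sizes below 0.85, the deltas and the dropout mechanism are assumptions, because the documents give none.

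The primary analysis remains valid under its own imputation assumption, and type I error is not inflated. The defect is one of interpretation, and it should be corrected because the correction is nearly free.

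**What to change.** Delete the condition in the Statistical analysis section. State that the missing-data sensitivity analysis of the 4-week CIS fatigue score will be done and reported whatever the primary p-value, with its assumptions fixed before unblinding.

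A suitable form is a delta-adjusted imputation in which the imputed CIS values are shifted separately by arm and in both directions, reported as a tipping point. The range of shifts can go in the SAP. The number with a missing 4-week CIS should be reported by arm, so that readers can judge how much the assumption matters.

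The cost is one change of wording and one extra analysis run. Sample size, alpha, power and the primary test do not change.

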### Power calculation

The sample size is based on the fatigue subscale score of the CIS at 4 weeks. In the present study, the power calculation is based on results from comparable studies with CFS patients where fatigue severity was determined with the CIS-fatigue scale [40]. If interleukin-1 plays a central role in CFS symptomatology, we expect a considerable reduction of fatigue following treatment. Assuming a large controlled effect size of 0.85, an alpha of 0.05 and a power of 0.80, 23 patients are needed in each arm of the study. The number of patients can be further reduced by using ANCOVA, with the outcome measure on the second assessment as the dependent measure, the baseline score as the covariate, and condition as the fixed factor. In this kind of trials, ANCOVA yields greater power compared to other statistical methods [39]. Based on the correlation between the pre- and post CIS fatigue scale, the sample size of 23 can be multiplied by 0.883 (1 to 0.342^2^). Including an assumed dropout rate of 20 percent, we will have to include 25 patients in each group to demonstrate a significant difference between the medication group and placebo.

## Discussion

This study will be the first randomized placebo-controlled trial to evaluate the effect of blocking IL-1 on symptoms in patients with CFS. Earlier studies investigated cytokine production to be of relevance in CFS patients, but conflicting results have been published [11, 13]. A possible explanation is that good controls have not been used in these studies, and cytokines were measured in peripheral blood instead of in tissues.

Blinding the study for anakinra is a difficult procedure because of the occurrence of local skin reactions in a significant amount of patients. To maintain the double-blind design of this trial, side effects will be evaluated by an independent PA. In earlier “double blind” trials, medication was injected in the presence of the main investigator [27]. The effect of anakinra will be measured up to 6 months after the start of treatment. In this manner, we can evaluate the long-term effect of blocking IL-1 for a short period. It will provide more insight into the best treatment for CFS patients when blocking IL-1 appears to be effective.

In conclusion, this study will provide more insight into the pathophysiology and treatment of patients with CFS. If an effective treatment can be found, this will drastically improve the quality of life in patients with this disabling disease.

### Trial status

Recruiting.

## Abbreviations

AE: adverse event
BDI: Beck Depression Inventory
CBT: cognitive behavioral therapy
CFS: chronic fatigue syndrome
CIS: Checklist Individual Strength
ECCF: Expert Center Chronic Fatigue at Radboud University Medical Center
EudraCT: European Drug Regulatory Affairs Clinical Trials
GCP: good clinical practice
GET: gradual exercise therapy
HAM-D: Hamilton Rating Scale for Depression
HPA-axis: hypothalamic-pituitary-adrenal-axis
IL-1: interleukin-1
IL-1Ra: interleukin-1 receptor antagonist
IL-8: interleukin-8
MINI: The Mini-International Neuropsychiatric Interview
PA: Physician Assistant
SCL-90: Symptom Checklist 90
s.c.: subcutaneously
SD: standard deviation
SF-36: Short Form 36
SFQ: Shortened Fatigue Questionnaire
SIP: Sickness Impact Profile
TNFα: tumor necrosis factor α
VAS: Visual Analog Scale
